### Measures

Sociodemographic data (e.g., age, sex and gender, occupation) and medical information (e.g., patient-, family-, and drug anamnesis, medication history and current medication, results of clinical diagnostics and clinical tests such as ECG and EEG) are extracted from patient records.

### Psychophysiological assessment and actigraphy

Psychophysiological measurements are conducted at baseline, after 3 weeks of intervention and at the end of the 6-week intervention period. These three measurements are acquired without simultaneous tVNS. In the pilot (*n* = 20), additional psychophysiological measurements will be additionally conducted immediately after starting the morning tVNS stimulation session at baseline and following 3 weeks of tVNS application. The measures encompass an N-Back task and a reward task. In the N-back task, which evaluates the working memory capacity, a sequence of stimuli is presented to the subjects, who indicate through pressing a button, if the current stimulus matches a stimulus presented N steps earlier in the sequence^38^. In AddVNS, the visual stimuli are capital letters (the consonants B, C, D, G, P, T, W). The reward task has been reported in earlier studies of our institute^39^. The variant that will be used in the AddVNS study comprises four conditions: a potentially rewarding response condition with a reward stimulus, a neutral response condition (neutral stimulus), a potential loss condition and a control condition without a response requirement (stimulus without response). After the presentation of the stimuli and a brief flash of light, the subjects must respond by pressing a button. If they respond fast enough, they will receive a financial reward (1 €) or a non-monetary reward (a green checkmark symbol). If the reaction is too slow, a red cross appears, which is followed by a financial loss (-1 €) in the loss condition. In the control condition, no flash is presented and therefore no reaction is required. An adaptive algorithm ensures that participants are successful in around 50% of reward trials. Pupil measurements and reaction times are recorded during the reward task. Furthermore, short measurements (e.g. resting state pupillometry, pupillometry during five separate light flashes, word-pairs association task) will be used as control conditions.

For the psychophysiology measurements, we use Biopac’s MP150 System (Goleta CA, USA, biopac.com) in our psychophysiology lab. Pupillometry is assessed with an inhouse Unity-based presentation environment (stimuli are presented on a screen in an Office) for an HTC Vive Pro Eye system with Tobii Eye-Tracking, with a sampling rate of 120 Hz (HTC Corporation, Taoyuan, Taiwan). During the psychophysiological measurements in our psychophysiology lab, the following parameters are assessed using the MP150 system with Bionomadix Wireless units: a 3-lead ECG with one electrode under the right collar bone, one under the left collar bone and one above the left-front side of the hip (LEAD II), respiration with a respiratory belt on the lowest part of the diaphragm, pulse plethysmography acquired on the left middle finger and a 3-lead electrogastrogram on the stomach area. The activity pattern and continuous physiology of participants over the 6-week intervention including the repeated psychophysiology lab session are measured using a wrist-worn actigraph (ActiGraph LEAP, Ametris, Pensacola FL), which provides continuous measures of activity, heart rate, oxygen saturation, and skin temperature, among others. The heart rate signal forms the basis for further processing, with the RR-intervals as inputs for segmented, sliding-window-based heart rate variability analyses (spectral metrics, statistical metrics, and respiratory-sinus arrhythmia-based metrics).

For pupillometry, the primary focus of the analyses will be on measures summarizing the pupillary light reflex (e.g., constriction velocity, amplitude), pupillary unrest (e.g., mean and variance metrics) during a 6-minute resting-state, mean pupil values during working memory blocks, and pupil responses during reward anticipation as in^40,41^. Pupillometric data will be pre-processed with linear blink-interpolation, smoothing and z-transformation, among others^40,41^, with in-house scripts in Matlab 2025 (The Mathworks Inc., Natick, Massachusetts, 2025). EGG will be spectrally analyzed according to consecutive 256s epochs, with 192s overlap according to the *Handbook of Psychophysiology*,* Chap. 12 – Levine et al.*^42^.

### MRI scans

Two identical MRI sessions are acquired. The first session is scheduled at baseline, the second one after the 6-week of tVNS. The elements of the MRI assessment are shared with the imaging protocols of our institute’s deep-phenotyping study BeCOME (Project No. 350 − 14)^43^. MRI protocols include an anatomical T1-weighted sequence, a diffusion tensor imaging (DTI) and an axial fluid-attenuated-inversion-recovery (FLAIR) sequence. Moreover, resting state functional MRI (rs-fMRI) and the following specific fMRI sequences and tasks are obtained:

(i)Neuromelanin (NM)-sensitive MRI: this sequence will be used to measure the functional and structural status of the locus coeruleus, the substantia nigra and the area tegmentalis ventralis (VTA). It is an established method used in the research of the noradrenergic and dopaminergic neurotransmission^44–47^. The NM-sensitive sequence will also allow to precisely localise these brainstem structures for the functional analyses.(ii)Brainstem-sensitive fMRI-BOLD sequences: This is a sequence for fMRI-BOLD time series aligned to methodological recommendations of a sequence and post-processing comparison for brainstem imaging^48^. It allows, in combination with appropriate post-processing, the investigation of the functional relationship between individual brainstem nuclei^48^.(iii)Reward anticipation task: This established task^43^ allows the quantification of three key circuits during reward anticipation (early activation of the ventral striatum, later activation of the salience network and deactivation of the default mode network). As described earlier for the reward task during psychophysiological measurements, a further stimulus type, which results in a small loss of money if performance is too low, will be added to the three established stimuli (possibility of winning money, verbal feedback, no possibility of winning). Overall, small symbolic play money sums with maximum total gains of 1–5 € will be used. The dynamic aspects of the task have been studied using combined fMRI/pupillometry experiments in healthy subjects^39^ and patients with major depressive disorder^49^. To allow for flexible secondary statistical methods, we will define between 2 and 5 regions-of-interest per network from large independent samples that have undergone the same task (e.g.^43^.(iv)Short imaging stress test (short-IST): This task is a reduced version of an imaging stress test^43,50^ that combines arithmetic calculation with (negatively feedback) evaluation. This reduced 10’ version presents 1-minute-episodes of arithmetic calculations with mild evaluation alternating with 40 s of pausing, causing marked autonomous nervous system (ANS) response that can be mapped to central ANS perception or regulation processes^51^.

rs-fMRI and reward-fMRI are carried out with simultaneous eye tracking and pupillometry (EyeLink 1000 Plus System with long range (MR) Mount, SR Research). Furthermore, heart and respiratory rate are recorded throughout the MRI scan using pulse plethysmography and a respiratory belt. No MRI contrast agent is injected.

### Blood-based multiomics

The collected blood samples will be used for genome-wide genotyping and epigenetic/DNA methylation analysis as well as mRNA sequencing, analysis of neuron-derived exosomes, cytokine and immune metabolite analysis, immune cell phenotyping and analysis of metabolic and endocrine markers. For more details on blood-based analyses, we refer the interested reader to the published protocol of DetECT study^52^, which proposes the same multiomics measures.

### Stool samples

Stool samples are collected at baseline and after 6 weeks of verum or sham tVNS using the Bunny Wipe Fecal Sample Collector System (Zymo Research). If tolerated by a participant, additional sample collection after three weeks of tVNS is performed. Stool samples will undergo shotgun metagenomic sequencing, as done in related studies, to enable taxonomic and functional characterization of the gut microbiome over time.

Clinical interviews are conducted at baseline, after 3 weeks of intervention and after 6 weeks of intervention. During these interviews, trained study personnel obtains the following scales: Montgomery–Åsberg Depression Rating Scale (MADRS)^64,65^, Hamilton Rating Scale for Depression with 21 items (HAM-D21)^66–68^ and Hamilton Rating Scale for Anxiety (HAM-A)^69^. The Global Assessment of Functioning (GAF)^70,71^ will also be obtained using information provided by the patient`s clinical ward team at the same time points. The MADRS (10 items) and the HAM-D21 are used to assess the severity of the present depressive episode. The GAF, which is a compound scale derived from the DMS-IV that rates global socioemotional impairment of patients with mental disorders, is used as a functionality proxy.

### Neuropsychological assessment and personality assessment

Neuropsychological assessment is carried out at baseline and after the 6-week intervention using the Cognitive Basic Assessment Test set (COGBAT)^72^ as well as the “Mehrfachwahl-Wortschatz-Intelligenztest” (MWT-B)^73^ and an episodic memory test^74^. The COGBAT was administered using the standardized software and hardware provided by the test distributor (Schuhfried). The MWT-B and the episodic memory test are administered in their respective standardized printed formats in accordance with the publishers’ guidelines.

Personality assessment is performed at baseline using the German short version of the Personality Inventory for DSM-5 (PID-5-BF + M) and the German short version of the Level of Personality Functioning Scale-Brief Form 2.0 (LPFS-BF 2.0)^75–77^. Both questionnaires can be filled out quickly by patients and allow a reliable assessment of personality traits. In the AddVNS study, PID-5-BF + M and LPFS-BF 2.0 will be used to investigate the role of personality traits in the depressive episode in the content of the biological effects of tVNS.

### Follow-up

To assess the long-term effects of tVNS, including the lasting self-reported clinical effects in e.g. the home environment after discharge from clinical care, we ask the participants to fill out self-rating questionnaires 6 and 12 weeks after the end of the intervention. At each of these two points, the questionnaires BDI-II, PHQ-9, PHQ-15, SHAPS-D, FLEI and WHODAS 2.0. are obtained. In case the participants have been discharged prior to the follow-up, they will receive the paper-pencil questionnaires (by mail) or be asked to complete them electronically after receiving a link via email, in accordance with our data protection and privacy policy.

### Sample size calculation

Earlier tVNS studies with a design similar to AddVNS, which have focused on clinical outcomes rather than biological ones, have shown low to moderate effect sizes^18,19,23,35^. Moreover, depression is a complex and multifactorial disease, which emerges through the long-time interaction between genetic predisposition and environmental factors^78^. Since no prior multi-omics studies on tVNS effects are available, the sample size calculation was based on the average effect sizes reported in existing clinical tVNS studies. This approach assumes that clinical efficacy reflects the aggregate downstream effects of multiple interacting biological pathways underlying tVNS and can therefore serve as a pragmatic proxy of expected average effect size of omics domains in the absence of direct multi-omics effect size estimates. Such an approach can be considered contemporary and appropriate for early-phase or exploratory multi-omics trials^52,79,80^. In addition, the AddVNS study incorporates an internal pilot phase. Should pilot data unexpectedly indicate that the main assumption regarding effect size is significantly inaccurate, sample size estimates will be updated prior to completion of recruitment, in line with established methodological recommendations^81,82^. Using a G-power calculation tool^83^, we estimated a sample size of *n* = 86 (ANOVA with repeated measures, 2 groups, effect size Cohen’s f = 0.25, significance level a = 0.05, power = 0.95, allocation in study arms 1:1, correlation between repeated measures = 0.3).

Based on prior experience with stimulation studies conducted at our clinic^52^, the AddVNS study anticipates a study discontinuation rate (including loss to follow-up) of approximately 30%. To account for this, we plan to recruit up to *n* = 112 participants, ensuring that at least *n* = 86 complete datasets are available for statistically meaningful analyses in accordance with the sample size calculation. Data from participants who discontinue the study will be included in the final analyses under an intention-to-treat framework. In addition, if more than 10% of data are missing, missing values will be handled using established imputation methods and the results will be compared with those obtained from the intention-to-treat analyses. Using heart rate variability-based stratification, among other psychophysiological and fMRI measured (e.g., pupil size), subgroup analyses will be performed.

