**Fig. 1 Fig1:**
[figure not shown]
Schematic diagram of participant timeline in the AddVNS study. Patient health questionnaire 9 and 15 (PHQ9 and PHQ15), Beck Depression Inventory II (BDI-II), Snaith-Hamilton-Pleasure-Scale (SHAPS), Rejection Sensitivity Questionnaire (RSQ), World Health Organization Disability Assessment Schedule 2.0 (WHODAS 2.0.), Montgomery–Åsberg Depression Rating Scale (MADRS), Hamilton Rating Scale for Depression with 21 items (HAM-D21), Hamilton Rating Scale for Anxiety (HAM-A), Global Assessment of Functioning (GAF), Pulse plethysmography (PPG), Personality Inventory for DSM-5 Brief form (PDI-5), functional MRI (fMRI). Created with Biorender.com.

Participants receive either tVNS or sham tVNS for 6 weeks in addition to treatment-as-usual (TAU). Psychophysiological assessments, clinical interviews, blood draws, and stool collection are scheduled at baseline as well as 3 and 6 weeks after tVNS start. A functional MRI (fMRI) session as well as an extensive neuropsychological assessment is performed at baseline and after 6 weeks post tVNS start. Additionally, a personality self-report assessment is acquired at baseline. Furthermore, participants are asked to complete self-rating questionnaires on a weekly basis. The optional questionnaire-based follow-ups are inquired 6 and 12 weeks after tVNS end. Study duration thus amounts to 8 weeks plus 12 weeks of follow-up.

The study will start with a pilot. Here, two additional psychophysiological measurements (amounts to a total of five measurement time points) will be conducted during tVNS stimulation up to 20 participants after the initial psychophysiological assessment at baseline and following 3 weeks of tVNS application. The objective of this pilot is to examine acute effects of tVNS on psychophysiological parameters, providing first insights into the potential mechanisms of action. Owing to the exploratory and first-in-field nature of this study, patient and public involvement was not included in the study design. The AddVNS study’s multi-omics read-outs are shown in Fig. 2.

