### Main hypotheses and statistical analyses

The focus of the statistical analyses in the AddVNS study is to examine the longitudinal changes between the two study arms (tVNS vs. sham tVNS) at the level of neurobiological readouts. Our aim is to identify parameter patterns that allow direct or indirect conclusions *primarily* about the biological effects of tVNS and *secondarily*, its clinical effects. Age, sex, socioeconomic status, BMI, smoking status, and pharmacological treatment (psychiatric and otherwise) as well as comorbidities will be integrated as covariates. Analyses will be performed regularly (e.g., after the pilot phase) as well as at the study’s end.

At the **neuroimaging level**, given the neuroanatomy of tVNS^16^ several functional readouts will be used for the study of tVNS effects over 6 weeks, contrasted against sham treatment. The general underlying hypothesis is that the 6-week stimulation course produces midterm-lasting functional effects that could underlie parallel or future clinical effects.

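### The sample size may be updated on an effect size seen in at most 20 pilot participants, an estimate too imprecise to confirm or overturn the planning assumption

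*Protocol article*

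**What the plan says.** The Sample size calculation section plans 86 complete datasets: repeated-measures ANOVA, two groups, Cohen's f = 0.25, alpha 0.05, power 0.95, correlation 0.3. Recruitment is up to 112. The section adds that "the AddVNS study incorporates an internal pilot phase" and continues: "Should pilot data unexpectedly indicate that the main assumption regarding effect size is significantly inaccurate, sample size estimates will be updated". The update is to happen before recruitment ends and "in line with established methodological recommendations". No outcome, threshold, direction or cap is given.

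The pilot's size appears in two places. The Study design section says the extra measurements "will be conducted during tVNS stimulation up to 20 participants"; the Psychophysiological assessment section says: "In the pilot (*n* = 20), additional psychophysiological measurements will be additionally conducted". Study design gives the pilot's objective as acute effects on psychophysiological parameters.

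Randomization and blinding says that all participants in a block receive the same intervention and that a new block starts only when the previous block's participants have finished. Main hypotheses and statistical analyses makes longitudinal change between arms the focus, and says: "Analyses will be performed regularly (e.g., after the pilot phase) as well as at the study’s end".

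**The concern.** An internal pilot can usefully check nuisance parameters such as variance, correlation and discontinuation. Here it is the effect size that is to be checked, and an arm contrast from about 10 patients per arm says little about it. A correct assumption could be judged wrong by chance, and the trial resized on noise.

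Two features of this trial weaken the pilot contrast further. The pilot was set up to look at acute effects, while f = 0.25 comes from clinical tVNS studies and the analysis targets change between arms over the 6 weeks. And because each block is a single arm and blocks run one after another, a pilot of 20 may hold few blocks, so that arm cannot be separated from block and calendar time.

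Resizing on an observed effect while keeping those patients in an unadjusted final test also raises type I error. How much depends on the rule, which is not stated.

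**Working it through.** **1. The plan's own figure.** The article does not state the number of measurements or the effect tested, so 86 cannot be reproduced uniquely. With f = 0.25, correlation 0.3 and power 0.95:
- group-by-time interaction: 76 (2 measurements) or 60 (3);
- between-group effect: 138 (2), 114 (3) or 86 (7).

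For the last case, the noncentrality is f²·N·m/(1+(m−1)ρ) = 0.0625 × 86 × 7/2.8 = 13.4, and power is 0.952. So 86 is not shown to be wrong. To stay neutral about its derivation, the check below scales the effect so that N = 86 gives exactly 95% power.

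**2. Calibration (normal approximation).** N = 4 × (1.960 + 1.645)²/d², with 3.605² = 13.0. At N = 86, d = 3.605/√(86/4) = 0.777. This is the effective standardized effect on whatever contrast was planned.

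**3. What 20 patients tell us.** The pilot z-statistic has mean 3.605 × √(20/86) = 1.74 and SD 1. Solving N again from the pilot estimate gives N = 20 × 13.0/z² = 260/z². With the planning effect exactly true:
- median: 260/1.74² = 86;
- lower quartile of N: z = 1.74 + 0.67 = 2.41, N about 45;
- upper quartile of N: z = 1.74 − 0.67 = 1.06, N about 230 (226 by simulation, which also squares wrong-sign estimates);
- N above 172 (more than doubled): |z| < 1.23, probability about 30%;
- N below 43 (less than halved): |z| > 2.46, probability about 24%;
- wrong sign: z < 0, probability about 4%.

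With the planned 30% discontinuation, about 14 of 20 complete. The interquartile range becomes about 40 to 272, with 33% more than doubled, 27% less than halved and 7% of the wrong sign.

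**4. Blocks (illustration; block size and number are not given).** Assume back-to-back blocks over 3 years (156 weeks) and 112 participants.
- If a block occupies 8 weeks: 156/8 gives about 19 blocks of about 6, so 20 patients span 3 to 4 blocks.
- If the 12-week follow-up also counts: 156/20 gives about 8 blocks of 14, so 20 patients span 1 to 2 blocks.

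Step 3 ignores any block effect and so flatters the pilot.

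**5. Type I error from resizing alone.** This was simulated under the null: pilot of 20, N re-solved from the observed effect and held within assumed limits, all patients in an unadjusted two-sided 0.05 test.

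| Limits on N (assumed) | Type I error |
|---|---|
| 86 to 112 | 5.2% |
| 86 to 172 | 5.5% |
| 86 to 344 | 5.8% |
| 22 to 172 (reduction allowed) | 6.2% |
| 22 to 1,000 (reduction allowed) | 6.7% |

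**The case against.** The update is a contingency, worded for an unexpected and marked discrepancy, and the study calls itself exploratory. This is a condensed article: the full research protocol is a supplement that is not shown, an analysis plan may exist, and the recommendations cited for the update cannot be seen. Any of them could supply a threshold, a cap or an adjusted test. That stands, and silence on error control is not held against the plan. It does not rescue the trigger: the article itself names effect size as the assumption to be checked, and the condition is judged on the same noisy pilot data. The exploratory label helps little, because the sponsor chose a 0.05 test with 95% power and treats 86 complete datasets as the target.

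Three stronger readings are tempting, and the documents do not support them.
- **Repeated testing at 0.05 without control.** A reader might infer this from the regular analyses. But alpha 0.05 appears only as an input to the sample size calculation, and nothing says that interim results count as findings or lead to stopping. If they did count, the error would be about 9.1% with looks at 20 and 86, and about 13.8% with five looks. Looks that lead to no decision leave the final test unchanged.
- **A far wider spread of N.** A simple two-sample formula at d = 0.5 puts the quartiles at about 80 and 1,400. But at its own planning value it gives 4 × 13.0/0.25 = 208, not 86, so it is not calibrated to this trial.
- **Certain harm.** No reduction, futility rule or early stop is described, so a cut or abandoned trial is a possibility, not a plan.

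**Conclusion.** The concern holds for the trigger. Even when the planning effect is exactly right, a pilot of 20 would suggest a total more than double or less than half of 86 in about 30% + 24% = 54% of cases. How many of these would prompt an update is unknown, since the article does not say what counts as markedly inaccurate. Discontinuation and few blocks make the estimate worse. The effect on type I error is real but modest, about 5.2% to 6.7%.

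These figures assume a normal approximation, independent patients, 1:1 allocation within the pilot, an effect scaled to 95% power at N = 86, and, for type I error, the limits on N shown above. They also assume that the internal pilot used for resizing is the pilot of up to 20 described elsewhere in the article, which is the natural reading.

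**What to change.** Replace the effect-size trigger. Re-estimate only from data pooled over arms, with labels withheld: variance, correlation between repeated measures, and discontinuation. Keep the planning effect size, and do not lower the planned recruitment of 112 on pilot results. Two details matter:
- Because f is already standardized, a pooled variance can change N only if the planning effect is also stated in the units of a named outcome. Otherwise only correlation and discontinuation act.
- Block-to-block variance should not be on the list. Each block is one arm, so unlabelled variation between blocks contains the treatment effect.

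State that any interim between-arm result is descriptive and that the 0.05 test is made once, at study end.

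If the sponsor wants to keep effect-based resizing, pre-specify the outcome, the decision rule, the cap and an adjusted final test (a combination test or the conditional error approach).

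The cost is a short wording change, reviewed by the ethics committee as the article requires for modifications. The downside is small: the sponsor gives up resizing on an early observed effect.

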### Study objectives

The primary hypothesis of our study is that tVNS induces biological and psychophysiological changes in patients with depression, and that the magnitude of these changes is associated with the antidepressant effects of tVNS. All collected data will be used to evaluate whether beneficial tVNS effects (in addition to TAU) can be predicted. Results will be presented on conferences and published in peer-reviewed journals and, if appropriate, on the Max-Planck-Institutes website in plain language for relevant groups (e.g., participants, physicians).

The main objective of the study is therefore to identify neuroimaging and psychophysiological changes associated with tVNS. The study’s secondary objective is the exploratory investigation of individual markers or clusters of clinical, psychometric, and biological markers which may relate to the course of tVNS in depressive patients receiving TAU (multiomics). Moreover, these parameters as well as the course of treatment (e.g. effects and side effects) will be correlated with the tVNS stimulation paradigm, such as current intensity and daily stimulation duration. The collected data will be used to develop predictive models aiming to identify factors associated with beneficial effects of tVNS in patients with depression.

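### The stated 95% power at n = 86 matches neither main readout as printed: without a nonsphericity correction it reproduces only as a group main effect over seven measurements

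*Protocol article*

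**What the plan says.** The Protocol article, Sample size calculation, gives n = 86 from a G*Power calculation: "ANOVA with repeated measures, 2 groups, effect size Cohen’s f = 0.25, significance level a = 0.05, power = 0.95", 1:1 allocation and a correlation of 0.3 between repeated measures. It does not say whether the effect tested is group, time or group x time. It gives no number of measurements and no nonsphericity correction (epsilon). The effect size is taken from clinical outcomes of earlier tVNS studies, whose effects the same section describes as low to moderate.

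Other sections fix what the calculation should serve:

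- Study objectives: "The main objective of the study is therefore to identify neuroimaging and psychophysiological changes associated with tVNS".
- Study design, text under Fig. 1, on MRI: "A functional MRI (fMRI) session as well as an extensive neuropsychological assessment is performed at baseline and after 6 weeks post tVNS start". That is 2 measurements.
- Psychophysiological assessment and actigraphy: "Psychophysiological measurements are conducted at baseline, after 3 weeks of intervention and at the end of the 6-week intervention period". That is 3 measurements. The two extra recordings are for up to 20 pilot participants only.
- Main hypotheses and statistical analyses: the focus is to "examine the longitudinal changes between the two study arms (tVNS vs. sham tVNS) at the level of neurobiological readouts". Clinical effects are placed second.

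**The concern.** In a repeated-measures power calculation, the effect tested and the number of measurements decide the answer as much as f and alpha do. The printed inputs do not return 86 for two or three measurements unless an unstated correction is added. The only schedule in the article that fits seven is the weekly self-rating (baseline plus six weekly ratings, which is my inference), and that is not a main readout. A group main effect is also not a comparison of change: it averages in the baseline, where randomised arms are expected to be equal.

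At stake is what the 95% figure can support. The section says that 86 complete datasets allow meaningful analysis in line with the calculation, and it plans to revise the sample size if pilot data contradict the assumed effect. Both need a defined test and a defined meaning of f. Without them, a null MRI or autonomic result could be given more weight than it can bear.

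**Working it through.** **Inputs** (all from Sample size calculation): 2 groups, f = 0.25, alpha = 0.05, target power 0.95, rho = 0.3, N = 86. The number of measurements m comes from the sections cited above: 2 for MRI, 3 for psychophysiology. Epsilon is taken as 1 because none is stated. Power comes from the noncentral F distribution.

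**Formulas (G*Power)**

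- Group main effect: lambda = N f² m / (1 + (m − 1) rho), df 1 and N − 2.
- Group x time: lambda = N f² m / (1 − rho), df m − 1 and (N − 2)(m − 1).

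**1. Reproducing 86.** Smallest even N for 95% power:

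| m | Group main effect | Group x time |
|---|---|---|
| 2 | 138 | 76 |
| 3 | 114 | 60 |
| 4 | 102 | 50 |
| 5 | 94 | 44 |
| 6 | 90 | 40 |
| 7 | **86** | 36 |
| 8 | 84 | 32 |

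For the main effect with m = 7, lambda = 86 × 0.0625 × 7 / 2.8 = 13.44 and power is 0.952. N = 84 gives 0.947.

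**2. The same test with the actual number of measurements, N = 86**

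- m = 2: lambda = 86 × 0.0625 × 2 / 1.3 = 8.27, power 81%.
- m = 3: lambda = 86 × 0.0625 × 3 / 1.6 = 10.08, power 88%.

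**3. Group x time at nominal f = 0.25, N = 86**

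- m = 2: lambda = 86 × 0.0625 × 2 / 0.7 = 15.36, power 97%.
- m = 3: lambda = 86 × 0.0625 × 3 / 0.7 = 23.04, power 99%.

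**4. What that f means with two measurements.** For a difference in change of D (in SD of a single measurement), the change score has variance 2(1 − rho), so lambda = N D² / (8(1 − rho)). Setting this equal to 2 N f² / (1 − rho) gives D = 4f = 1.0 SD. As a plain two-group difference, f = 0.25 is d = 2f = 0.5.

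**5. If f = 0.25 is read as d = 0.5 at week 6 with equal baselines** (assumption), N = 86, rho = 0.3:

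- Change score: lambda = 86/4 × 0.25 / 1.4 = 3.84, power 49%. Across d = 0.2 to 0.5 the range is 12% to 49%.
- Week-6 difference adjusted for baseline: lambda = 86/4 × 0.25 / (1 − 0.09) = 5.91, power 67%.
- Group x time over 3 measurements: 39% if the difference grows linearly, 51% if it is complete by week 3.
- At correlation 0.5, change score gives 63% and baseline adjustment 75%. At 0.7 they give 84% and 89%.

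**6. Smallest detectable difference at N = 86, rho = 0.3**, solving the two lambdas of step 5 for d: by change score, 0.72 SD at 80% power and 0.93 SD at 95%; with baseline adjustment, 0.58 SD and 0.75 SD.

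**7. Sensitivity to epsilon.** For group x time, lambda and both df are multiplied by epsilon. With m = 3 and epsilon about 0.62, the required N is also 86 (0.60 gives 88, 0.64 gives 84). With m = 2 there is a single contrast over time, so epsilon is 1 and the answer stays 76.

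**The case against.** The strongest reply is that the planned comparison is group x time. For that test, at the f and correlation as printed, the requirement is 76 for MRI and 60 for psychophysiology, so 86 is enough. This stands as arithmetic. It does not explain where 86 comes from, and with two measurements it holds only if a 1.0 SD difference in change is expected.

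Second, an unreported epsilon of about 0.62 with three measurements gives 86 for group x time, which is the psychophysiology schedule and the stated comparison. It cannot be excluded, so the seven-measurement reading is an inference about how 86 arose and not a documented fact. It does not help MRI.

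Third, the study is exploratory, calls its effect size a pragmatic proxy, allows a pilot-based update, and refers to a full protocol in the supplement that is not shown. The effect tested and the number of measurements may be given there. That excuses the brevity. It does not make the printed inputs yield 86 for a readout measured twice.

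A reader might go further and infer that the trial misses 95% power whatever the test, or that 138 or 114 is the right sample size. The documents do not support either. Those two figures belong to a main-effect test that does not suit the stated comparison, and the shortfall disappears under group x time at nominal f.

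**Conclusion.** The point holds in this limited form. As printed, 95% power at 86 is not reproduced for either main readout without an unstated correction, and for MRI no such correction can supply it. What 86 delivers depends on a choice the article does not make:

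- 81% (MRI) and 88% (psychophysiology) for the main-effect test that yields 86;
- 97% and 99% for group x time at nominal f, which for MRI means a 1.0 SD difference in change;
- about 49% by change score, or 67% with baseline adjustment, for a 0.5 SD difference.

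The last line rests on reading f = 0.25 as d = 0.5 and on the article's correlation of 0.3; a higher correlation raises it. The first two rest on epsilon = 1. The allowance for discontinuation and the wording of the primary objective are separate matters and are not used here.

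**What to change.** In Sample size calculation, base the power statement on the planned comparison: group x time, or the week-6 difference adjusted for baseline. Use 2 measurements for MRI and 3 for psychophysiology. State the effect tested, any epsilon, and what f = 0.25 means in SD units. Replace the single 95% figure with the power, or the smallest detectable difference, at N = 86 for each main readout. For MRI with baseline adjustment and correlation 0.3, for example, that would be 67% power for 0.5 SD, or 0.58 SD detectable with 80% power. Show the range over plausible correlations, and use the same definition for the pilot-based update.

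The cost is a reworded paragraph and probably a less favourable power figure. It needs no extra patients and no change to the assessment schedule.
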